## Abstract

**Background:**

Emerging evidence suggests modulating the microbiota in the large bowel of patients with chronic kidney disease (CKD) through pre- and/probiotic supplementation may inhibit the development of key nephrovascular toxins. To date, quality intervention trials investigating this novel treatment in CKD are lacking. The aim of SYNERGY is to assess the effectiveness of synbiotics (co-administration of pre- and probiotics) as a potential treatment targeting the synthesis of uremic toxins, specifically, indoxyl sulphate (IS) and p-cresyl sulphate (PCS).

**Methods/design:**

Thirty-seven patients with moderate to severe CKD (Stage IV and V, pre-dialysis) will be recruited to a double-blind, placebo-controlled, randomised cross-over trial. Patients will be provided with synbiotic therapy or placebo for 6 weeks, with a 4 week washout before cross-over. The primary outcome is serum IS, total and free (unbound) concentrations, measured using ultra-performance liquid chromatography. Secondary outcomes include serum PCS, total and free (unbound) concentrations; cardiovascular risk, measured by serum lipopolysaccharides, serum trimethylamine-N-oxide (TMAO) and inflammation and oxidative stress markers; kidney damage, measured by 24 hour proteinuria and albuminuria, estimated glomerular filtration rate and renal tubule damage (urinary kidney injury molecule-1); patients’ self assessed quality of life; and gastrointestinal symptoms. In addition, the effects on the community structure of the stool microbiota will be explored in a subset of patients to validate the mechanistic rationale underpinning the synbiotic therapy.

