## Methods/design

### Study aim

The aim of the *SYNbiotics: Easing Renal failure by improving Gut microbiologY* (SYNERGY) study is to investigate the effects of synbiotics (co-administration of pre- and probiotics) as a potential treatment for reducing IS and PCS production in the CKD population. The primary hypothesis is that synbiotic supplementation in patients with Stage IV or V CKD (pre-dialysis) will be effective in reducing accumulation of total and free (unbound) concentrations of IS. The secondary hypotheses for SYNERGY include: a) reduction in total and free concentrations of PCS; b) reduction in cardiovascular risk- measured by reduced endotoxemia, trimethylamine-N-oxide (TMAO) and inflammatory and oxidative stress markers; c) reduction in kidney damage- measured by proteinuria and albuminuria and renal tubule damage (urinary kidney injury molecule-1 (Kim-1)); d) improvement in quality of life (QOL); and e) improvement in gastrointestinal (GI) symptoms.

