### Primary outcome

#### Serum indoxyl sulphate

Venous blood will be collected following an overnight fast at 7 time points throughout the study, see Table 2. Samples will be centrifuged at 3000 rpm for 10 mins before being stored at −80°C. Samples will be batched and sent for analysis of serum concentration of IS, total and free, using an ultra-performance liquid chromatography (UPLC) and fluorescence detection method. This recently validated method will allow for low limits of detection down to 0.1 μmol/L and has been described in detail by Pretorius et al. [39]. This method will also be followed for PCS.

**Table 2 T2:** SYNERGY data collection schedule

		**Run-in Week −2**	**Intervention A & B**		
			**Baseline**	**Mid point**	**End point**
			**Week 0 & 11**	**Week 3 & 14**	**Week 6 & 17**
**Serum uremic toxins**	Indoxyl sulphate (free and total)	X	X	X	X
	P-cresyl sulphate (free and total)	X	X	X	X
**Cardiovascular risk**	Oxidative stress		X		X
	Inflammation		X		X
	Endotoxemia (lipopolysaccharide)		X		X
**Kidney damage**	24 hr albuminuria and protienuria		X		X
	Kidney injury molecule-1		X		X
	Estimated glomerular filtration rate	X	X		X
**Dietary**	Diet history interview	X			X
	24 hr recall		X	X	
	24 hr urinary urea nitrogen		X		X
**Quality of life**	Short Form-36				X
**Gastrointestinal symptoms**	Gastrointestinal symptom rating scale	X		X	X
**Gut microbiota**	Fecal sample (optional)		X		X
**Compliance**	Pill count			X	X
**Dose escalation**				X	

Participants will be provided with a standard evening meal preceding their overnight fast before each blood collection. This is a precautionary measure to minimise any potential residual influences of the macronutrient distribution of proximal meals on participants’ serum IS and PCS levels.

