### Statistical analysis

Preliminary data from a cohort of CKD Stage IV-V (pre-dialysis) patients recruited from the same Nephrology department were used for power calculations. The mean serum concentration of IS in this population was 14 μmol/L with a mean intra individual standard deviation of 4 μmol/L between 3 measurements over a 6 week period (unpublished data from [name] and [name]). With 1:1 randomisation, SYNERGY will require 24 participants to complete the study. This sample size is based on a 30% reduction in IS levels; alpha of 5% and power of 90%. Allowing for a 20% drop out and using the adjustment factor 1/1(1-υ)^2^, a total of 37 participants will be recruited. This magnitude of change is related to a significant improvement in kidney function [56]. Furthermore, a reduction in IS concentration of this size has been achieved in previous probiotic intervention studies and is therefore considered a realistic target [57].

The primary analysis of IS concentrations will be undertaken using an independent t-test with treatment sequence allocation as the independent variable and the difference between serum concentrations measured after the first and second treatment as the dependent variable [58]. Secondary analysis of the primary outcome will include mixed modelling to account for missing data and to determine whether there is a dose dependent effect of the synbiotics.

In addition to the widely used diversity metrics and analysis tools available via QIIME, permutational multivariate analysis of variance (PERMANOVA) will be conducted on the genus level operational taxonomic units (OUT) tables to test the relationships between the stool microbiome and the primary and secondary outcomes of the study. Constrained ordination methods, such as analysis with respect to instrumental variables, will also be carried out [59].

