Previous studies in pre-dialysis populations suggest a high incidence of antibiotic prescription secondary to high comorbidity burden, susceptibility to urinary tract infections, and prophylactic use for surgical procedures. Because this is a proof-of-concept study and the use of antibiotics may confound the mechanisms underpinning the synbiotic therapy, sensitivity analyses will be undertaken including and excluding patients prescribed antibiotics during either intervention arm. In addition, further analysis will be undertaken to assess whether there is a treatment order effect. The null hypothesis will be rejected at the 0.05 level. The statistical analyses will be performed using Stata (version 12, 2012, Statacorp, College Station, TX).

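### Total and free IS are both the primary outcome, but no rule links them at the single 0.05 level, and the sample size covers one unlabelled IS measure

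*Protocol article*

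**What the plan says.** Three places in the protocol article make both measures primary:

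- Abstract, Methods/design: "The primary outcome is serum IS, total and free (unbound) concentrations".
- Study aim: the primary hypothesis is that the supplement "will be effective in reducing accumulation of total and free (unbound) concentrations of IS".
- Primary outcome, Serum indoxyl sulphate: the samples are analysed for "serum concentration of IS, total and free", and neither measure is ranked first.

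The Statistical analysis section then speaks of IS as one quantity. Its planning inputs are "The mean serum concentration of IS in this population was 14 μmol/L" and a "mean intra individual standard deviation of 4 μmol/L", and "This sample size is based on a 30% reduction in IS levels", with alpha 5%, power 90%, 24 completers and 37 recruited. The primary analysis is an independent t-test between treatment sequences on the difference between the two post-treatment values. The only decision rule is "The null hypothesis will be rejected at the 0.05 level". The section gives no order of testing, no split of alpha and no statement that both results are needed.

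**The concern.** Total and free IS are separate measurements with separate distributions. One t-test on one difference cannot serve both, so the natural reading is one test for each. The article does not say how two results become one conclusion.

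This matters if the two measures disagree. As the text stands, a significant result on either could be reported as the primary result once the data are seen, and the false-positive risk of that practice exceeds the stated 5%. A reader also cannot tell which measure the stated power belongs to, because the mean and SD are unlabelled and no figures are given for a second variable.

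**Working it through.** **Inputs, all from Statistical analysis.** Mean 14 μmol/L; intra-individual SD 4 μmol/L; 30% reduction; alpha 5% (two-sided assumed, since the article does not say); power 90%; 1:1 allocation to sequence; 24 completers; 20% drop-out; 37 recruited.

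**Step 1. Reproduce the sample size for one variable.**

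- Treatment effect: 0.30 × 14 = 4.2 μmol/L.
- SD of a within-patient difference: 4 × √2 = 5.66.
- The mean period difference has opposite signs in the two sequences, so the contrast between sequences is 2 × 4.2 = 8.4.
- Normal approximation, per sequence: 2 × [(1.960 + 1.282) × 5.66 / 8.4]² = 9.5, rounded up to 10, so 20 in total.
- Noncentral t: 11 per sequence, 22 in total (power 91.2%).
- The stated 24 is within two patients of this, so the figure is reproduced for one variable.
- Recruitment by the article's factor: 24 / 0.8² = 37.5, against 37 stated.

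**Step 2. Power for one variable at 24 completers.** The standard error of the contrast is 5.66 × √(2/12) = 2.31 and the noncentrality is 8.4 / 2.31 = 3.64. With 22 degrees of freedom, power is 93.5%.

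**Step 3. Two variables, each tested at 0.05.** The article's t-test was simulated with 12 patients per sequence and 100,000 runs per correlation. The correlations are assumptions. Joint power further assumes that both measures have the standardised effect of step 1.

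| Correlation | False positive if either counts | Power if both are required |
|---|---|---|
| 0 | 9.8% | 87.5% |
| 0.5 | 9.2% | 88.8% |
| 0.7 | 8.4% | 89.6% |
| 0.8 | 7.8% | 90.1% |
| 0.9 | 7.1% | 91.1% |
| 0.95 | 6.6% | 91.8% |

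Check at correlation 0: 1 − 0.95² = 9.75%, and 0.935² = 87.4%. If both are required, the false-positive rate is at most 5%, because a false claim needs a 5% test to fail on a measure with no effect.

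**Step 4. Allow for the recruitment margin.** At the stated drop-out, 37 × 0.8 = 29.6, so 29 or 30 patients complete. With 29 completers, power for one variable is 97.1%. Power for both under independence is 0.971² = 94.2% to rounding, with the same equal-effect assumption.

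**Step 5. How far the equal-effect assumption carries.** The inputs imply a within-patient coefficient of variation of 4/14 = 29%. For a 30% reduction and 24 completers, the noncentrality is 0.6 / (CV × √2 × √(2/12)) = 1.039 / CV. If the second measure had a CV of 35% or 40% (illustrative values), its own power would be 81% or 70%, and joint power could not exceed that. The article gives no mean or SD for a second measure, so its power can be neither confirmed nor refuted.

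**Step 6. Alternative of splitting alpha.** At 0.025 for each measure, 24 completers give 88.2% power, and 90% needs 26 completers. By the article's factor, 26 / 0.64 = 40.6, so 41 recruits.

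**The case against.** The strongest reply has four parts.

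- **The wording may mean both.** The primary hypothesis joins the two measures with the word and. If both must succeed, the 5% is safe. This stands as a possible reading, but the article does not make it a success rule.
- **Testing each measure at 0.05 is inferred.** The article has one general sentence on the rejection level. This is correct, and the error-rate figures apply only if success on either measure counts. But nothing in the text excludes that, and one t-test cannot cover two variables.
- **It may be settled elsewhere.** A condensed article can leave the rule to a full protocol or analysis plan that is not shown. That would excuse silence on detail. Here, though, the article itself fixes a two-variable primary outcome, one rejection level and a one-variable sample size, and these do not fit together without a linking rule.
- **The inflation is an upper bound and the study is proof-of-concept.** Two measures of one analyte from one sample may well be strongly correlated, so 9.8% is the extreme. The rate is still above 5% at 0.95, and the article claims 5% and 90% for itself.

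A reader might go further and infer that either the 5% or the 90% must fail. The article does not support that. With both required, an equal standardised effect and a correlation of about 0.8 or more, both figures hold at 24 completers. At the 29 or 30 completers that the recruitment target implies, joint power exceeds 90% even under independence. Figures that start from exactly 90% for each measure would understate power, since the article's inputs give 93.5%.

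**Conclusion.** The point holds as a missing link between two primary measures, not as a demonstrated loss of power. If either measure can carry the primary claim, the false-positive rate is about 6.6% to 9.8% for correlations from 0.95 down to 0, against the stated 5%. If both are required, the error rate is controlled, and joint power at 24 completers is about 87% to 92% on the equal-effect assumption. The 90% is supported for one IS measure only, and the article does not say which. The results assume two-sided testing and the t-test between sequences; the correlations and the second measure's effect are not in the article.

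**What to change.** In Statistical analysis, state which IS measure the 14 and 4 μmol/L describe. Name that measure as the single primary variable, tested at 0.05, and test the other at 0.05 only if the first is significant. State that the sample size and power refer to the first variable only. Align the abstract, study aim and outcome section with this.

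The change takes a few sentences and holds the 5% error rate across both measures. The 24 completers and 37 recruits stay as they are, and the lead variable keeps its 93.5% power at 24 completers. The small downside is that the second measure cannot be claimed alone if the first fails. Splitting alpha would avoid that downside but needs 26 completers for 90% power. Requiring both would also hold the 5%, but its power cannot be stated without a mean and SD for the second measure.

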**Discussion:**

IS and PCS are two novel uremic toxins implicated in both cardiovascular disease (CVD) and progression of CKD. Preliminary studies indicate that synbiotic therapy maybe a promising strategy when considering a targeted, tolerable and cost-efficient therapy for lowering serum IS and PCS concentrations. This trial will provide high quality ‘proof-of-concept’ data to elucidate both the efficacy of synbiotic therapy for lowering the toxins and whether reductions in serum IS and PCS translate into clinical benefits. Considering the potential of pre- and probiotics to not only shift toxin levels, but to also impede CVD and CKD progression, SYNERGY will provide vital insight into the effectiveness of this innocuous nutritional therapy.

**Trial Registration:**

Universal Trial Number: U1111-1142-4363. Australian New Zealand Clinical Trials Registry Number: ACTRN12613000493741, date registered: 2^nd^ May 2013.

## Background

In recent years, an appreciation for the role of the gut microbiota in health and disease has gained momentum, with microbial modulating therapies emerging in mainstream medicine [1]. Within the discipline of Nephrology, the evidence supporting the role of the kidney-gut axis in uremia is building [2]. In fact, it is now clear that the dysbiotic gut microbiotia observed in chronic kidney disease (CKD) [3] produce key nephrovascular toxins, indoxyl sulphate (IS) and p-cresyl sulphate (PCS) [4].

There is convincing evidence demonstrating dose-dependent nephro- and cardiovascular toxicities of IS and PCS in both *in vitro* and animal studies [5-7]. Further, in the past decade there has been a surge of observational studies describing these toxins and their associations with increased cardiovascular disease (CVD), kidney disease progression and all-cause mortality in the CKD population [8-12]. This growing body of observational literature warrants the need for more conclusive findings from intervention studies to elucidate whether there is a causal role of IS and PCS in the cardiorenal milieu, or whether they are in fact biomarkers *in vivo*.

A number of therapeutic opportunities for targeting IS and PCS have been proposed, including inhibition of colonic bacterial biosynthesis (protein restriction and microbial modulating therapies), suppression of absorption (oral adsorbents), augmentation of clearance (enhanced dialysis) and modulation of cellular pathways (organic anion transporters and antioxidants) [13]. Many of these therapies remain limited to experimental studies, have unfavourable side effects or a high cost burden preventing their translation to clinical research. In particular, oral adsorbents have been extensively studied, with promising improvements in both cardiovascular risk [14] and kidney function [15] following reductions in serum IS. Nonetheless, a recent Phase III trial (n = 2035), Evaluating Prevention of Progression In Chronic Kidney Disease (EPPIC), demonstrated no difference between placebo and intervention (AST-120) in CKD progression. Interestingly, post-hoc analysis suggested poor compliance may have contributed to the negative outcome [16]. Microbial modulating therapies, in the form of pre- and probiotcs, however, present themselves as a promising treatment given their low cost and innocuous nature. The potential benefit and definition of pre- and probiotics are outlined in Table 1[17,18]. These therapies have been summarised by a systematic review and meta analysis, which suggested an overall benefit for reducing the production of IS and PCS by first altering the microbiota community in the large bowel and thereby the metabolic activity and formation of these metabolites within the colon [19]. However, this review highlighted the body of evidence was weak due to poor study design, suboptimal methodologic quality, significant trial heterogeneity, and lack of scientific rationale for each study’s supplement selection (probiotic strains, prebiotic varieties and dosing). In addition, none of the trials evaluated in this review were undertaken in the pre-dialysis population where it may have the greatest therapeutic benefit for delaying CKD progression, nor did they investigate the effect of lowering the toxins on clinically relevant markers and outcomes.

**Table 1 T1:** Mechanisms underpinning the scientific rationale for the selection of the synbiotic formulation targeting the production of indoxyl sulphate and p-cresyl sulphate

**Prebiotics ***“**A selectively fermented ingredient that allows specific changes, both in the composition and/or activity in the gastrointestinal microflora that confers benefits upon host wellbeing and health” *[17]	Selectively support the colonization of probiotics
	Increase the carbohydrate:nitrogen ratio in the colon favouring beneficial saccharolytic vs. proteolytic fermentation
	Decrease colonic pH (through short chain fatty acid production) thereby impairing protein degradation with inactivation of pH sensitive proteases
	Increase the colonic transit time, thereby decreasing time for bacterial production and intestinal absorption of indoxyl sulphate and p-cresyl sulphate
	Enhance bacterial growth with increased uptake of the amino acids for bacterial biosynthesis and therefore less substrate for protein fermentation
**Probiotics***“Live microorganisms which when administered in adequate amounts confer a health benefit on the host” *[18]	Acid and bile resistance to ensure survival through the upper gastrointestinal tract
	Competitive exclusion of indoxyl sulphate and p-cresyl sulphate producing bacteria (through competition for essential nutrients and luminal and epithelial binding sites)
	Direct bacterial antagonism via inhibitory substance production (such as biosurfactants, hydrogen peroxide, and bacteriocins)
	Immunomodulation via immune cell activation resulting in indirect inhibition of pathogenic bacteria

For these reasons, high quality studies are needed to address 1) the efficacy of synbiotic therapy for reducing IS and PCS and 2) whether such reduction in toxin concentrations is associated with clinical benefit. Answers to these fundamental questions will ascertain the clinical applicability of synbiotic therapy in the CKD setting; and also provide new insight into how the microbiota may be redirected to promote better clinical management of CKD.

## Methods/design

### Study aim

The aim of the *SYNbiotics: Easing Renal failure by improving Gut microbiologY* (SYNERGY) study is to investigate the effects of synbiotics (co-administration of pre- and probiotics) as a potential treatment for reducing IS and PCS production in the CKD population. The primary hypothesis is that synbiotic supplementation in patients with Stage IV or V CKD (pre-dialysis) will be effective in reducing accumulation of total and free (unbound) concentrations of IS. The secondary hypotheses for SYNERGY include: a) reduction in total and free concentrations of PCS; b) reduction in cardiovascular risk- measured by reduced endotoxemia, trimethylamine-N-oxide (TMAO) and inflammatory and oxidative stress markers; c) reduction in kidney damage- measured by proteinuria and albuminuria and renal tubule damage (urinary kidney injury molecule-1 (Kim-1)); d) improvement in quality of life (QOL); and e) improvement in gastrointestinal (GI) symptoms.

### Study design

SYNERGY is a single-centre, double-blind, placebo-controlled, randomised cross-over trial. Participants will undergo a 2 week run-in period, followed by randomisation to either synbiotic supplements or placebo for 6 weeks. Thereafter, participants will undergo a further 4 week washout period followed by crossover to the alternative intervention (Figure 1). The 4 week washout is considered sufficient for the pre-intervention microbiota to re-establish [19].

**Figure 1 F1:**
[figure not shown]
SYNERGY study schema.

### Ethical considerations

Ethical approval has been granted through Metro South Human Research Ethics Committee and the University of Queensland Human Research Ethics Committee. Further, Therapeutic Goods Administration has approved the synbiotic supplements under the Clinical Trials Notification Scheme.

### Target population

The trial will recruit Stage IV-V non-dialyzed CKD patients. Inclusion criteria will include patients under the care of a Nephrologist at the Princess Alexandra Hospital with an estimated glomerular filtration rate (eGFR) between 10-30 ml/min/1.73 m^2^, aged ≥18 years and able to provide informed consent. Patients will be excluded if they meet any of the following criteria: previous renal transplant; receiving/or have received radiation to the bowel or large bowel resection; consumed pre- or probiotics or antibiotic therapy within 1 month of study commencement; medically diagnosed irritable bowel syndrome, Crohn’s disease or ulcerative colitis; non-English speaking; likely to receive a transplant or progress to dialysis within 6 months, as determined by treating physician; severely malnourished (Subjective Global Assessment: C); or having had a clinically significant change to their immunosuppressant dose within 6 months (determined by the medical team). The latter criterion is to mitigate any risk associated with severely immunocompromised patients, although increased risk even in the critically ill is thought to be minimal [20].

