### Supplement dosing and duration

The synbiotic intervention will be a daily dose of 15 grams of prebiotics, including a combination of 3 different types of fibres, and the probiotic component will include 90 billion colony-forming units (CFU) from 9 different strains across the Lactobacillus, Bifidobacteria and Streptococcus genus. There is no consensus as yet on adequate dosing or duration of synbiotics due to the diversity of GI survival rates of probiotic strains and the different characteristics of prebiotic varieties, such as their bifidogenic capacities [33]. Nevertheless, the available evidence suggests that there maybe be a threshold dose and duration required to see a benefit for lowering IS and PCS production [19]. The dosing of pre- and probiotics used in SYNERGY is based on previous successful trials [30,36,37]. However, in order to minimise the side effects reported in previous studies, such as flatulence and bloating [38], the synbiotics will commence at half dose for the first 3 weeks.

The durations of most intervention studies in this area have been ≤4 weeks, with one study demonstrating no benefit comparing 4, 8 and 12 week intervention periods [37]. The intervention period for SYNERGY is a 6 week duration to allow time for dose escalation, minimise symptom burden and establish whether there is a dose-dependent and sustained benefit of the therapy.

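### The exclusion meant to protect severely immunocompromised patients tests only for a recent immunosuppressant dose change; no listed criterion asks about current immune status

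*Protocol article*

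**What the plan says.** The Target population section gives a list of exclusions, any one of which bars entry. The last is "having had a clinically significant change to their immunosuppressant dose within 6 months (determined by the medical team"). It is the only one given an immune-related rationale: "The latter criterion is to mitigate any risk associated with severely immunocompromised patients". The same sentence adds that "increased risk even in the critically ill is thought to be minimal".

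The other exclusions are a past kidney transplant; bowel irradiation or large bowel resection; prebiotics, probiotics or antibiotics in the preceding month; irritable bowel syndrome, Crohn's disease or ulcerative colitis; not speaking English; expected transplant or dialysis within six months; and being "severely malnourished (Subjective Global Assessment: C").

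Table 1 in the Background defines probiotics as "Live microorganisms which when administered in adequate amounts confer a health benefit on the host". Under Supplement dosing and duration the probiotic part is "90 billion colony-forming units (CFU) from 9 different strains" per day, and "the synbiotics will commence at half dose for the first 3 weeks". Under Study design, each participant takes one intervention for six weeks and then has a washout, "followed by crossover to the alternative intervention".

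**The concern.** The stated aim and the criterion do not describe the same patients. The aim is about who is severely immunocompromised when they enter. The criterion is about whether a dose has recently been altered. Recent change is a reasonable partial proxy, because it picks up patients just started on treatment or just escalated. It says nothing about a patient whose regimen has not changed, or whose immune deficit does not come from drugs.

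At stake is the entry check on a live-organism product. In a parallel-group trial a patient admitted through this gap might have received placebo only. In this crossover every completer takes the synbiotic, so the assigned sequence changes only when the exposure happens. The point does not bear on the sample size, the primary analysis or the error rates.

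**Working it through.** No figure in the plan has to be reproduced. The check is a reading of the criterion against its purpose, followed by a search for anything else that closes the gap.

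**Step 1: which patients the dose-change item catches.**

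| Patient at screening | Severely immunocompromised? | Caught by the dose-change item? |
|---|---|---|
| Immunosuppressant started or clearly escalated in the last 6 months | Possibly | Yes |
| Unchanged regimen for more than 6 months, with severe immunocompromise | Yes | No |
| Severe immunocompromise from a cause other than drugs | Yes | No |
| Dose clearly reduced in the last 6 months | Perhaps less than before | Yes, since no direction of change is stated |

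Rows two and three are the gap. They do not assume that a stable dose implies severe immunocompromise; they say only that the item cannot detect it where it exists.

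**Step 2: whether another exclusion covers rows two and three.** The exclusions for kidney transplant, Crohn's disease, ulcerative colitis and severe malnutrition may remove some of these patients, but on other grounds. The antibiotic exclusion removes some patients recently treated for infection, which is again not a test of immune status. The remaining items are unrelated. The reference to the medical team's judgement attaches to the dose change and gives no general discretion over immune status.

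**Step 3: whether a safeguard elsewhere in the article covers them.**

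- Ethical considerations: ethics approval and regulatory notification apply to the trial and are not a check on each patient.
- Supplement dosing and duration: the half-dose start is justified by flatulence and bloating.
- Gastrointestinal symptoms: symptom scores are collected for safety, but during the study.
- Safety and adherence: serious adverse event reporting and the review of blood and urine results also act after enrolment.

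These lower the residual risk. None screens immune status at entry.

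**Step 4: exposure of one completer.** Inputs from Supplement dosing and duration: 90 billion CFU per day at full dose, 6 weeks (42 days), half dose for the first 3 weeks (21 days).

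- If the half dose applies to the probiotic part: 21 × 45 + 21 × 90 = 945 + 1,890 = 2,835 billion CFU.
- If it applies only to the fibre: 42 × 90 = 3,780 billion CFU.

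Every completer has this exposure, so it shows what an admitted patient would receive and does not measure the defect. The article gives no prevalence of such patients and no probability of harm, and none is assumed.

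**The case against.** The strongest reply is that the article claims only mitigation. It does not say that every severely immunocompromised patient is kept out, and a partial safeguard described as mitigation is not contradicted by being partial. The article also rates the added risk as minimal even in the critically ill, so a narrow precaution may be proportionate. Every participant is under a nephrologist's care at the study hospital, and other exclusions remove some of the patients in question. A condensed article may leave finer eligibility detail to a full protocol that is not shown. Finally, a clause resting on the medical team's judgement has no threshold or test, whereas the present item has a defined event and a time window.

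Much of this stands. The wording is not a contradiction, the risk rating cannot be reassessed from this document and is accepted, and the number affected may be zero. These points are why the matter is minor.

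They do not close the gap. The sponsor chose to screen for this group and named this item as the means. The article states both the criterion and its rationale, and one falls short of the other, so this is not simply a detail left out of a summary. The looseness of the added clause is a real limitation, but the existing item already relies on the same team's judgement of what is clinically significant, and it would stay in place.

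**Conclusion.** The concern holds as a minor safety point. The dose-change exclusion serves its stated purpose only in part: a patient severely immunocompromised on an unchanged regimen, or for a non-drug reason, meets no exclusion on that account and could be enrolled. How many such patients would present is unknown.

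The conclusion rests on the exclusion list as printed. If the full protocol contains an explicit immune-status criterion, the point reduces to correcting the article's description. Correcting it is optional but cheap.

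**What to change.** In Target population, keep the dose-change item unchanged and add to the exclusions: *or currently severely immunocompromised, as determined by the medical team*. The rationale sentence would then apply to both items.

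The cost is one more screening judgement per patient, made by the team that already judges the dose-change item, and possibly the loss of a few otherwise eligible patients from a single-centre trial recruiting 37. The sample size calculation and the analysis need no change.
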